### 2.10. Assessment

All assessments will be conducted before and after the intervention. A clinical assessment will be also conducted to classify the disease staging with the HY scale, which will be used only at the beginning due to its classificatory nature. Due to the amount of tests and measures, and to prevent participant fatigue, the assessments will be over 2 days.

### 2.11. Primary Outcome Measures

Musculoskeletal function, functional mobility, and balance were chosen as primary outcome measures because they are directly affected by the progression of the disease and are susceptible to interventions.

Muscle strength will be assessed with an isokinetic dynamometer (Biodex, System4Pro™, Shirley, NY, USA). The contraction type will be set to the concentric/concentric mode, the angle velocities selected will be 90°/s and 120°/s [21], and the protocol will include two repetitions throughout maximal range of motion for ankle plantarflexor and dorsiflexor muscles, knee and hip flexor and extensor muscles bilaterally, with a 2-min break in between repetitions [22].

The Five-Times-Sit-to-Stand functional test will be used to assess the strength and power of the lower limbs [23]. Participants will start the test in a seated position and will then be instructed to stand up and sit down five times on an armless chair (43 cm) as fast as possible, with the arms crossed on the chest [23]. The movement is repeated five times in a row without interruptions, being timed throughout the test [23]. The necessary equipment includes a fixed, armless, four-legged chair with back support [23]. If the person takes longer than 16 s to perform the task, they are categorized as being at a risk of falls [23].

Functional mobility will be further assessed with the Timed “Up and Go” Test (TUG), which consists of timing how long the person takes to stand up from a standard armchair (approximately 46 cm high), walk for 3 m, turn, walk back to the chair, and sit down again [24]. If they take longer than 16 s to complete the test, they are categorized as being at a risk of falls [23].

The 6-m walk test will be used to assess functional gait. It will be performed in a 10-m course, timing the walk on the 6 middle meters, excluding the acceleration and deceleration phases [23,25]. Three attempts will be collected at participants’ self-selected walking speeds; then the mean distance walked (18 m) will be divided by the sum of the three trial times. A speed slower than 0.98 m/s indicates a risk of falls for people with PD [23].

The Berg Balance Scale (BBS) will be used to assess stability and anticipatory postural control, as well as the association of strength, dynamic balance, and flexibility necessary for postural control [26]. The BBS has 14 items, each one scored from 0 to 4, thus totaling a maximum score of 56 points [26]. Higher values indicate better performance [26]. Conducting the BBS requires a chronometer, a ruler, one armless chair, and one armchair and it takes about 20 min to be performed [26,27]. Results lower than 47 points indicate a risk of falls for people with PD [23].

Postural control during quiet standing will be assessed with a force platform (model OR-06, AMTI, Watertown, MA, USA). The protocol requires the participant to stand still for 30 s, with arms at the side, for three times in each foot position, in the following order: (i) feet together with eyes open; (ii) feet together with eyes closed; (iii) semi-tandem feet with eyes open; (iv) semi-tandem feet with eyes closed.

The mean result of the three trials in each position will be used to assess postural control based on the sway of the center of pressure, calculated in the anteroposterior and mediolateral directions. The total length of the center of pressure displacement, anteroposterior and mediolateral amplitudes of the center of pressure, and the area of displacement of the center of pressure will be obtained from analyses made in MATLAB 9.1.0 (The MathWorks Inc., Natick, MA, USA).

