## Abstract

Introduction: The complications from Parkinson’s disease (PD) are directly related to decreased muscle function, balance deficits, and independence loss. Practicing aquatic exercises can minimize these symptoms and slow disease progress. Objective: To develop a Multicomponent Aquatic Training (MAT) protocol for people with PD between stages 1 and 4 of the Hoehn and Yahr scale. Methods: The protocol is for a single blind controlled clinical trial. The sample will comprise of people with PD between stages 1 and 4 in Hoehn and Yahr scale, divided into a control group and MAT group (who will participate in the MAT). Musculoskeletal function, functional mobility, and balance will be the primary outcomes of interest, assessed with an isokinetic dynamometer, the Five-Times-Sit-to-Stand test (FTSST), the Timed “Up and Go” test (TUG), the 6-m gait speed test, the Berg Balance Scale (BBS), and a force platform. Quality of life (QOL), activities of daily living (ADL), and motor aspects will be the secondary outcome measures, assessed with the Parkinson’s Disease Questionnaire (PDQ-39) and Unified Parkinson’s Disease Rating Scale (UPDRS), sections II and III. The MAT will be 12 weeks long, with two 50-min sessions per week. The outcome measures will be assessed before and after the interventions. Discussion: This study is expected to establish parameters to prescribe and monitor a MAT program for people with PD in stages 1 to 4 in the Hoehn and Yahr scale, respecting individual progress and assisting the professionals in their procedure with these people.

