### 2.15. Statistical Analysis

The normality of data distribution will be assessed with the Shapiro–Wilk test and expressed as mean (±standard deviation), minimum, and maximum values. The variables analyzed will be compared between initial and final assessment and between groups with a mixed-model ANOVA. It is recommended that the effect size and statistical power be also published.

SPSS 20.0 statistical software will be used in all the analyses. A *p*-value < 0.05 will be used to determine significant differences.

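### Three whole domains are primary with no deciding variable, contrast or success rule, so the chance of a false positive primary result is several times the nominal 5%

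*Protocol article*

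**What the plan says.** Section 2.11 sets the primary outcomes at the level of domains: "Musculoskeletal function, functional mobility, and balance were chosen as primary outcome measures because they are directly affected by the progression of the disease". The Abstract lists the instruments: "assessed with an isokinetic dynamometer, the Five-Times-Sit-to-Stand test (FTSST), the Timed “Up and Go” test (TUG), the 6-m gait speed test", then the Berg Balance Scale (BBS) and a force platform, which makes six.

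Section 2.11 gives the detail for two of them.

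- **Strength.** The muscles are "ankle plantarflexor and dorsiflexor muscles, knee and hip flexor and extensor muscles bilaterally", and "the angle velocities selected will be 90°/s and 120°/s". The torque parameter to be analysed is not named.
- **Force platform.** There are four stance conditions (feet together or semi-tandem, eyes open or closed). "The mean result of the three trials in each position will be used to assess postural control", and the measures are "The total length of the center of pressure displacement, anteroposterior and mediolateral amplitudes of the center of pressure, and the area of displacement".

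Section 2.15 compares the variables over time and between groups with a mixed-model ANOVA, and says that a p-value below "0.05 will be used to determine significant differences". It does not say which ANOVA effect decides.

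Section 2.14 gives 30 participants (15 per group) for an effect size of 0.25 on an F distribution, type I error 0.05 and power 0.84. It names no outcome.

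**The concern.** A type I error of 5% describes one test. Here the primary set holds at least one variable from each of six instruments, and possibly several dozen. Nothing says which result, or how many, would count as success on the primary outcome. After the data are in, any significant variable in any domain could be reported as a primary finding, and the 5% would not describe the chance of that happening by luck.

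The choice of primary outcome is a protocol matter. The article does not leave it to another document: it has a section for it and fills that section with three domains.

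**Working it through.** **1. The plan's own sample size.** The inputs from section 2.14 are f = 0.25, alpha = 0.05 and N = 30 in 2 groups. Section 2.10 gives m = 2 measurements. For the group x time interaction, λ = f²·N·m/(1−ρ) = 0.0625 × 30 × 2/(1−ρ) = 3.75/(1−ρ), tested on F(1, 28). The pre-post correlation ρ is not stated.

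- ρ = 0.6: λ = 9.375, power 0.840. This reproduces the stated 0.84.
- ρ = 0.5: λ = 7.5, power 0.753.

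(Three measurements at ρ = 0.5 also give 0.841, but the trial has two.) So N = 30 is the size for a single test at 0.05, under an unstated ρ of 0.6.

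**2. Number of primary variables, from section 2.11.**

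- Every combination: strength 6 muscle groups × 2 sides × 2 velocities = 24; sit-to-stand, TUG, gait speed and BBS = 4; sway 4 measures × 4 stances = 16. Total 24 + 4 + 16 = 44.
- Strength pooled over sides and velocities: 6 + 4 + 16 = 26.
- One variable per instrument: 6.

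**3. Chance of at least one p<0.05 on group x time when training has no effect.** For k independent tests this is 1 − 0.95^k, and 1 − 0.975^k if only results favouring training count. For correlated variables I used simulation (15 per group, equal correlation r between variables; r is assumed).

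| Variables | r | Any direction (nominal 5%) | Favouring training (nominal 2.5%) |
|---|---|---|---|
| 6 | 0 | 26.5% | 14% |
| 6 | 0.5 | 21% | 10% |
| 26 | 0 | 74% | 48% |
| 26 | 0.5 | 48% | 25% |
| 44 | 0 | 89.5% | 67% |
| 44 | 0.5 | 61% | 31% |
| 44 | 0.8 | 29–30% | 15% |

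The expected number of false positives among 44 null tests is 44 × 0.05 = 2.2 at any correlation.

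**4. Power of the possible remedies, N = 30, f = 0.25.** By the formula in step 1, f = 0.25 corresponds to a between-group difference of 1.0 SD with equal baselines.

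| Test | ρ = 0.5 | ρ = 0.6 |
|---|---|---|
| Group x time at 0.05 | 0.753 | 0.840 |
| Group x time at 0.05/3 (strictest Holm step, three primaries) | 0.581 | 0.695 |
| ANCOVA on baseline at 0.05, λ = 7.5/(1−ρ²), F(1, 27) | 0.86 | 0.91 |
| Follow-up difference, no baseline adjustment, λ = 7.5, F(1, 28) | 0.753 | 0.753 |

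**The case against.** Four points can be made in the plan's defence.

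**The count is not fixed.** Section 2.11 describes how strength and sway are measured; it does not say that each side, velocity and stance is a separate endpoint. This stands. A reader might infer that there are at least 44 primary variables, but 44 is one reading. Pooling gives 26 or fewer, and several torque parameters would give more.

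**A false positive in favour of training is not shown to be likely.** This also stands. Left and right limbs, two close velocities and four sway measures from one recording should be well correlated, and a two-sided count includes results against training. At r = 0.5 the chance of a result favouring training among 44 variables is 31%, and at 0.8 it is 15%. The article supports several times the nominal rate, not more likely than not.

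**An unadjusted test of every variable is not stated.** Section 2.15 gives a threshold and is silent on adjustment, and a multiplicity procedure may sit in an analysis plan that is not shown. It is tempting to read the section as committing to unadjusted tests, or as letting any of the three ANOVA effects count as success, but the text says neither. This removes the charge of a stated unadjusted rule. It does not supply the missing deciding variable.

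**The aim is largely developmental.** The Abstract and Conclusions speak of developing a programme and its parameters. However, the Discussion also aims to determine effects on muscle function, balance and mobility, and section 2.14 sets a type I error and power. The article therefore presents a test of effect.

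**Conclusion.** The point holds in a limited form. The protocol fixes its primary outcome as three domains and gives no deciding variable, contrast or success rule, while its sample size covers one F test at 0.05 tied to no outcome.

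Even one variable per instrument gives a false positive chance of 21% at correlation 0.5, about four times the nominal 5%. If all 44 combinations are analysed, the chance is between 30% and 90%. These figures assume that each variable is tested on group x time at 0.05 without adjustment, and that correlations are equal and lie in the ranges shown; the article states none of this. They describe chance alone. Allocation by patient preference (section 2.9) can add bias in either direction, and none of the figures includes it.

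**What to change.** Name one primary variable, for example TUG or BBS, and one contrast: the between-group difference adjusted for baseline, either by ANCOVA or as the group x time interaction. Test it at 0.05 and make all other variables secondary, without confirmatory claims. Tie the sample size to that variable and state the assumed pre-post correlation. An unadjusted follow-up difference should not be used, because it would carry baseline differences from preference allocation into the result.

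If all three domains must stay primary, name one variable in each and test them in a fixed order at 0.05, or by Holm.

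The change needs protocol and registry wording, and section 2.1 already provides for reporting changes to the ethics committee and the registry. The price is that fewer results can be called confirmatory. With group x time at N = 30, the single or first test keeps power 0.75–0.84 and the strictest Holm step falls to 0.58–0.70, for a pre-post correlation of 0.5–0.6. ANCOVA for the same effect gives about 0.86–0.91. This corrects multiplicity only; bias from preference-based allocation remains.

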### 2.12. Secondary Outcome Measures

Quality of life, motor function, and activities of daily living will be assessed as secondary outcome measures, as they are strongly influenced by the primary outcome measures.

Quality of life will be assessed with the Parkinson’s Disease Questionnaire (PDQ-39) [28,29]. The questionnaire has 39 questions divided into eight dimensions, namely: mobility, activities of daily living, emotional well-being, stigma (which assesses social difficulties in PD), social support, cognition, communication, and bodily discomfort [28,29]. The total score ranges from 0 to 100—the lower the score, the better the perception of health status [28,29].

Motor function and activities of daily living will be assessed with the Unified Parkinson’s Disease Rating Scale (UPDRS), sections II and III [30]. The UPDRS is an assessment scale for the patients’ signs, symptoms, and certain activities based on self-report and clinical observation [30]. It has 42 items distributed into four parts: mental activity, behavior, and mood (I); activities of daily living (II); motor examination (III); and drug therapy complications (IV) [30]. Each item scores from 0 (tending to normal) to 4 (greater impairment from the disease) [30].

Adherence and dropouts will also be collected to determine the tolerability and satisfaction of participants in the MAT.

### 2.13. Other Outcome Measures

The AP and HR will be measured before and after every assessment, and before and after every MAT session.

### 2.14. Sample Size

A sample size calculation was used to determine the number of participants required for the present study. The calculation was based on the prevalence of PD in Curitiba, Paraná. The sample calculation was performed using GPower 3.1 software, which stipulated a minimum sample of 30 individuals, assuming an effect size of 0.25 on a probability distribution F, whose value consisted of a mean distance between the sample mean and the population mean; a Type I error equal to 0.05 and analysis power equal to 0.84. Thus, the study will require 30 individuals with PD—15 allocated in the MAT group, and 15 in the control group. However, an extra 10% of participants will be added in order to avoid possible drop outs.

### 2.15. Statistical Analysis

The normality of data distribution will be assessed with the Shapiro–Wilk test and expressed as mean (±standard deviation), minimum, and maximum values. The variables analyzed will be compared between initial and final assessment and between groups with a mixed-model ANOVA. It is recommended that the effect size and statistical power be also published.

SPSS 20.0 statistical software will be used in all the analyses. A *p*-value < 0.05 will be used to determine significant differences.

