### 2.5. Multicomponent Aquatic Training (MAT)

The MAT was developed with PD patients classified between stages 1 to 4 in HY scale as the target population. The individuals allocated to the MAT group will be enrolled in a 12-week program with two 50-min sessions per week with at least 72 h between sessions, totaling 24 sessions.

The activities will take place in the pool at the Ana Carolina Moura Xavier Rehabilitation Hospital Center, in Curitiba, Paraná, Brazil. Due to the size and depth of the pool (10.75 m × 2.90 m; and 1.10 m deep), the groups will be limited to no more than six participants at a time. The pool will be kept at a mean temperature of 33 degrees Celsius.

Despite training being carried out in groups, there will be an experienced physical therapist and three physical therapy students in the pool to assist and instruct the patients while performing the exercises. Hence, individual attention will be provided, minimizing the risk of incidents in the water. There will also be another two physical therapy students outside the pool to provide support. These professionals will also record the arterial pressure (AP) and heart rate (HR) before and after the training, also being available in case any participant requires help during the intervention.

All training sessions will be separated as follows: functional mobility training and adjustment to the water (about 10 min); strength and muscle power exercises (about 10 min); balance or neuromotor exercises (about 20 min); and relaxation/cooldown (about 10 min). The MAT is described in detail in Annex 1, organized according to Israel’s five phases for learning aquatic motor skills [19], namely: (1) description of the activity, (2) main physical and thermal properties of the water involving the immersed body, (3) parameters of exercise progression, (4) transference of skills to land, and (5) classification of mobility in the ICF domains of activities and participation.

The training will be approached by progressively increasing volume and intensity to stimulate the participants’ neuroplastic potential [20]. Accordingly, every 4 weeks, training will be adjusted, with an increase in the degree of difficulty and complexity of the exercises. Table 1 describes the order and organization of the activities per week and intervention varieties, specifying which mobility/adjustment, muscle strength, balance, and relaxation training should be used.

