### 2.6. Control Group

The participants allocated to the control group will be instructed not to change their usual activities throughout the study. Once the experimental period is completed, the intervention will be offered to the control participants free of charge.

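### MAT is given in shared pool classes and control is not, yet the named ANOVA and the 0.84 power treat all 30 participants as independent; the error is modest and depends on an unstated class correlation

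*Protocol article*

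**What the plan says.** Section 2.15 (Statistical Analysis) names the test: "The variables analyzed will be compared between initial and final assessment and between groups with a mixed-model ANOVA". The only factors mentioned are time and group.

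Section 2.14 (Sample Size) reports a G*Power calculation "assuming an effect size of 0.25 on a probability distribution F", with "a Type I error equal to 0.05 and analysis power equal to 0.84", "which stipulated a minimum sample of 30 individuals". The split is "15 allocated in the MAT group, and 15 in the control group", and "an extra 10% of participants will be added in order to avoid possible drop outs". It gives no class size, ICC, design effect or pre/post correlation.

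Section 2.5 describes MAT as group training, two sessions a week for 12 weeks. Because of the pool's dimensions, "the groups will be limited to no more than six participants at a time". One physical therapist and three students are in the water.

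Section 2.6 gives the other arm no classes: "The participants allocated to the control group will be instructed not to change their usual activities throughout the study". Section 2.10 sets two assessments, before and after the intervention.

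**The concern.** With a cap of six, 15 people need at least three classes (15/6 = 2.5, rounded up). People who train together share sessions, pace, peers and staff, so their changes may be more alike than those of people in different classes. Controls have no such grouping. The design is therefore clustered in one arm only, which is called partially nested.

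A mixed-model ANOVA on time and group handles the two measurements within a person, but not similarity between people in the same class. Any positive class correlation makes the MAT mean less precise than the ANOVA assumes. The error is anti-conservative and falls on the trial's main comparison: the interval is too short, the false-positive rate exceeds 5%, and the stated power is too high. Class membership must be noted while the sessions run, because it may not be recoverable later.

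**Working it through.** **Inputs from the article.** N = 30 (15 + 15), f = 0.25, alpha = 0.05, power 0.84 (2.14); two assessments (2.10); class size at most 6 (2.5); controls ungrouped (2.6).

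**Assumptions not in the article.** Pre/post correlation rho of 0.5 or 0.6; class ICC of the change score from 0.01 to 0.10, with 0.20 as an extreme; three stable classes of five.

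**Step 1: reproduce 0.84.** For the group-by-time interaction with k = 2 groups and m assessments, the noncentrality is lambda = f² × N × m / (1 − rho), with degrees of freedom (k − 1)(m − 1) and (N − k)(m − 1).

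- m = 2, rho = 0.6: lambda = 0.0625 × 30 × 2 / 0.4 = 9.375 on 1 and 28 df; power 0.840.
- m = 2, rho = 0.5: lambda = 0.0625 × 30 × 2 / 0.5 = 7.5; power 0.753.
- m = 3, rho = 0.5: power 0.841, but the article plans two assessments.

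So 0.84 is what a formula for independent participants returns, with no design effect in it. With two assessments it needs rho of about 0.6.

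**Step 2: add classes in the MAT arm only.** With two assessments, the group-by-time test is a t test on change scores. With c = 5 per class, the MAT-arm design effect is DE = 1 + (c − 1) × ICC. The variance of the difference changes from (1 + 1)/15 to (DE + 1)/15, so the standard error ratio is √((DE + 1)/2) and lambda is divided by (DE + 1)/2. Example at ICC 0.05: DE = 1 + 4 × 0.05 = 1.20, ratio √1.10 = 1.049, lambda = 9.375/1.10 = 8.52, power 0.80.

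False-positive rates come from simulating change scores under no effect (200,000 trials per row) and applying the ordinary test.

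| ICC | DE | True SE / reported SE | False-positive rate of named test | Power, rho 0.6 | Power, rho 0.5 |
|---|---|---|---|---|---|
| 0 | 1.00 | 1.00 | 5.0% | 0.84 | 0.75 |
| 0.01 | 1.04 | 1.01 | 5.2% | 0.83 | 0.74 |
| 0.05 | 1.20 | 1.05 | 6.2% | 0.80 | 0.71 |
| 0.10 | 1.40 | 1.10 | 7.4% | 0.77 | 0.67 |
| 0.20 | 1.80 | 1.18 | 10.0% | 0.70 | 0.61 |

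The power columns keep 28 df and treat the ICC as known. Uneven classes of 6, 6 and 3 change little: at ICC 0.05, DE is 1.22, the SE ratio is 1.05 and the simulated false-positive rate is about 6.3%.

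**Step 3: what if the class variance is estimated from the data?** A class-means test with Satterthwaite df, at the effect that gives 0.84 under independence, has simulated power of 0.72 at ICC 0, 0.71 at 0.01, 0.67 at 0.05 and 0.62 at 0.10. Three classes also estimate the variance poorly. The between-class component is zero or negative when an F variable on 2 and 12 df falls below 1/(1 + 5 × ICC/(1 − ICC)). That probability is about 60% at ICC 0 and about 52% at ICC 0.05.

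**The case against.** **The class correlation may be small, or the classes may not be stable.** Section 2.5 sets a capacity limit and does not say that a participant stays in one class; rotation would weaken the clustering. It also promises individual attention. Section 2.7 has participants individually accompanied, and Appendix A adjusts speed to each person's exertion rating and makes balance progression depend on each person's skill. No difference in staffing between classes is described. All of this stands. It is why the result is conditional and why the range starts at 0.01. At ICC 0 the problem disappears.

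**A short article may leave random effects to a fuller document.** This stands in part, and a missing model specification alone would be no finding. But the article does commit itself to a named test and to a power of 0.84, and that figure comes from an independent-participant formula.

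**Stronger readings that the documents do not support.**

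- A reader might infer that clustering costs 17 to 18 points of power, from 84% to 66–67% at ICC 0.05. It does not. The class-means test has only 72% power at ICC 0, so about 12 points come from its few degrees of freedom and only about 5 from the correlation.
- A reader might want to replace 0.84 with one fixed value, such as 81% or 66%. Both rest on rho of 0.6, which section 2.14 does not state. At ICC 0.05, moving rho from 0.6 to 0.5 takes power from 0.80 to 0.71, a larger shift than the ICC causes.
- A reader might argue that preference allocation sorts people into classes. In section 2.9, preference decides MAT or control, not the class slot. Preference allocation is a separate source of bias, and a class term does not address it.

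**Conclusion.** The point holds as a modest, conditional correction. The group delivery, the ungrouped control arm, the two-factor ANOVA and the independence behind 0.84 are all in the article or follow from its figures. The direction of the error is clear whenever the class ICC is positive, but the documents do not fix its size.

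For stable classes and an ICC of 0.01 to 0.10, the interval for the MAT effect is about 1% to 10% too short, the nominal 5% test runs at about 5.2% to 7.4%, and power falls by about 1 to 7 points from 0.84. The power figures are also conditional on rho of about 0.6. The gap between rho 0.6 and rho 0.5 (0.84 against 0.75) is larger than the clustering loss anywhere in that ICC range, so the power statement needs both assumptions made explicit.

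**What to change.** **Section 2.15.** Record the pool class of each MAT participant, and say whether membership is fixed or may change. Report the group-by-time result with the MAT-arm variance multiplied by 1 + (m − 1) × ICC, where m is the class size, at an ICC stated in advance, with a sensitivity range of 0.01 to 0.10. A partially nested model, with class random in the MAT arm only and small-sample degrees of freedom, may be added as a sensitivity analysis. The text should say that three classes estimate the class variance poorly and that a class-based test has only about 72% power even at ICC 0 (under the assumptions that give 0.84 otherwise).

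**Section 2.14.** State that 0.84 assumes independent participants, give the pre/post correlation behind it, and report the lower power at the assumed ICC.

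**Cost.** One extra data field, a few sentences, a slightly wider interval for the MAT effect and a less favourable power figure. The change requires no extra participants or staff if the lower power is accepted and reported. Restoring the nominal variance would take about 18 MAT and 15 control participants at ICC 0.05 (15 × 1.20 = 18), or 21 and 15 at ICC 0.10 (15 × 1.40 = 21), before dropout.

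### Section 2.15 never names group-by-time as the deciding test of MAT; the two comparisons it does name are not the treatment effect

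*Protocol article*

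**What the plan says.** Section 2.15 describes the comparison in one sentence: "The variables analyzed will be compared between initial and final assessment and between groups with a mixed-model ANOVA". The decision rule is a p-"value < 0.05 will be used to determine significant differences". On reporting it adds: "It is recommended that the effect size and statistical power be also published". It does not mention the group-by-time term.

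Other sections bear on how this is read:

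- Section 2.14 sets the sample size "assuming an effect size of 0.25 on a probability distribution F", with "a Type I error equal to 0.05 and analysis power equal to 0.84", giving "15 allocated in the MAT group, and 15 in the control group". It does not say which ANOVA term the 0.25 belongs to.
- Section 2.1 has two assessments, at baseline and at three months.
- Section 2.9 allocates by patient preference, not at random.
- Section 2.3 admits HY stages 1 to 4. Section 2.10 records the stage at the start ("A clinical assessment will be also conducted to classify the disease staging with the HY scale") for classification only.

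**The concern.** A group-by-time ANOVA gives three p-values for each outcome. The time term averages the change over both groups, so it also contains any practice gain on repeated performance tests. The group term averages baseline and final values, so it contains any baseline difference and only half of any effect present at follow-up. The interaction, which with two assessments is the between-group difference in change, is the one that answers the trial's question.

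The text names the first two comparisons, applies one threshold, and does not say which result decides. A significant time or group term would therefore meet the stated rule and could be reported as evidence for MAT. The design is exposed to both problems: people who choose pool training may differ at baseline from those who do not, and the timed, strength and balance tests are repeated in everyone.

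**Working it through.** **Inputs.** From the document: N = 30 (15 per group), m = 2 assessments, alpha = 0.05, effect size 0.25 (read as Cohen's f). Assumed: pre-post correlation rho, varied from 0.5 to 0.8; equal SD at both assessments; a 0.5 SD baseline gap and a 0.3 SD common gain as illustrations. All tests are F with 1 and 28 df, and power comes from the noncentral F with parameter λ.

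**Step 1: reproduce the plan's figure.** For the time or the interaction term, λ = f²·N·m/(1 − rho) = 0.0625 × 30 × 2/(1 − rho) = 3.75/(1 − rho).

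- At rho = 0.6, λ = 9.375, power is 0.840 and the minimum N is 30. This matches section 2.14.
- At rho = 0.5, power is 0.753 and N = 38 would be needed for 0.84.
- For the group term, λ = 3.75/(1 + rho). Power is 0.46 down to 0.27 over rho 0 to 0.9, and at least 72 participants would be needed.

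The stated N of 30 thus fits the time and interaction terms equally well and does not fit the group term. Section 2.14 does not settle which term decides.

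**Step 2: put f on the outcome scale.** In a 2 × 2 layout a between-group difference in change of δ gives interaction effects of δ/4 per cell, so f = δ/(4·SD) and f = 0.25 means δ = 1.0 SD.

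**Step 3: compare the terms.**

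- *Group term, no MAT effect, persistent 0.5 SD baseline gap.* The averaged values differ by 0.5 SD with variance (1 + rho)/2 per person. λ = 0.5²/[(1 + rho)/2 × 2/15] = 3.75/(1 + rho).
- *Group term, true 1.0 SD effect at follow-up, no baseline gap.* Averaging over the two assessments leaves 0.5 SD, so λ is the same. The group term cannot tell these two situations apart.
- *Time term, no MAT effect, 0.3 SD gain in both groups.* λ = 0.3² × 30/[2(1 − rho)] = 1.35/(1 − rho).
- *Interaction, true 1.0 SD effect.* λ = 3.75/(1 − rho).

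| rho | Group term: 0.5 SD gap and no effect, or 1.0 SD effect and no gap | Time term: 0.3 SD common gain, no effect | Interaction: 1.0 SD effect |
|---|---|---|---|
| 0.5 | 0.333 | 0.355 | 0.753 |
| 0.6 | 0.315 | 0.426 | 0.840 |
| 0.7 | 0.300 | 0.535 | 0.927 |
| 0.8 | 0.286 | 0.708 | 0.987 |

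In a simulation with no MAT effect (rho 0.6, 20,000 runs), the interaction stayed at about 5% under a 0.5 SD baseline gap, a 0.5 SD common change, or both.

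**Step 4: ANCOVA as the alternative.** With groups comparable at baseline, ANCOVA of the final value on baseline has error variance (1 − rho²), against 2(1 − rho) for change. At rho 0.6 that is 0.64 against 0.80, and power for 1.0 SD is 0.91 against 0.84. At rho 0.8 it is 0.993 against 0.987. If a preference-driven gap simply persists, ANCOVA is biased by (1 − rho) × gap. At rho 0.6 with no MAT effect, that is 0.4 × 0.5 = 0.20 SD for a 0.5 SD gap (about 10% significant in simulation) and 0.40 SD for a 1.0 SD gap (about 21%). The interaction stays near 5% in both.

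**Step 5: power as a reported result.** If power is computed from the observed F(1, 28), it is fixed by the p-value: about 0.51 at p = 0.05 and 0.25 at p = 0.20. If the planned power is meant, section 2.14 already gives it.

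**The case against.** The strongest reply is that section 2.15 simply lists the two factors of a group-by-time design. A mixed ANOVA with those factors normally produces the interaction, and nowhere does the article say that a main effect will be taken as the MAT effect. That stands: the model does not lack the right term. What remains is that the text does not say which term decides, and the sample-size section does not supply the answer.

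Three stronger readings are tempting, and the document does not support them.

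- *The analysis ignores baseline.* It does not. Baseline is one level of the time factor, and with two assessments the interaction compares change scores. Baseline is only not a covariate.
- *ANCOVA should be the sole test.* Its precision gain assumes comparable groups, which preference allocation does not secure, and step 4 shows the error it can bring when a gap persists. If groups regress toward a common mean, the ranking can reverse. The choice is a judgement, and the interaction is defensible here.
- *The plan wants post-hoc power instead of a confidence interval.* The text asks for effect size as well, does not say observed power, and rejects no interval.

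A condensed article may also leave covariates and intervals to a fuller plan, so their absence is not the finding. They appear below only as part of a complete statement of the test.

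**Conclusion.** The point holds as a badly fixed decision rule, not as a wrong model. The two comparisons section 2.15 names are not the treatment effect, and the one that is goes unnamed. If either were read as the MAT effect, about 29–33% of trials would show a group difference from a persistent 0.5 SD baseline gap alone, and about 35–71% a time difference from a 0.3 SD common gain alone. The group term would also detect a true 1.0 SD effect only 29–33% of the time, against 75–99% for the interaction.

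These figures rest on rho between 0.5 and 0.8, which the document does not give; 0.6 is the value that reproduces its own N = 30 and power 0.84 with two assessments. The sizes of the gap and of the common gain are illustrations. No analysis choice removes confounding by preference.

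**What to change.** Amend section 2.15 to state that:

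1. The test of MAT for each outcome is the between-group difference in change (group-by-time), adjusted for HY stage and reported with a 95% CI. With two assessments this is a regression of change on group and stage.
2. Time and group main effects and within-group changes are descriptive only.
3. An ANCOVA of the final value on baseline value and HY stage is a sensitivity analysis, because with non-randomised groups the two estimates can differ and neither removes confounding by preference.
4. The effect size is reported with its 95% CI in place of statistical power.

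Section 2.14 should also say that f = 0.25 refers to the interaction and give the correlation assumed.

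The cost is wording only: no extra participants, visits or measurements, since HY stage is already collected. Entered as a linear term, stage uses one degree of freedom; at rho 0.6 that moves interaction power from 0.840 to 0.839 even if stage explains nothing. As a four-level factor it would use three.
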